### Design

This knowledge mobilization study uses a pragmatic cluster-randomized controlled trial (C-RCT) design, with embedded process evaluation. Such design will allow the measurement of clinical efficacy and costs of a multimodal intervention to improve PVC-related adverse events as such as PVC-BSI and phlebitis. We will compare outcomes and costs from implementation of CPGs. The embedded process evaluation will elicit the variable contexts of implementation, the barriers and enablers encountered, the response by stakeholders, and the resources required for implementation. The multicenter nature of the study, with the inclusion of hospitals with different organizational characteristics and located in different geographic areas, will enhance the diversity of the sample and thus its external validity. Reporting of this trial will adhere to the CONSORT statement and its extension to C-RCTs [31].

### Setting

The study will be conducted in five public hospitals with diverse characteristics within the Spanish National Health System, including one reference hospital and four acute care hospitals. Twenty wards will be selected and randomly allocated to either the intervention or control groups. The intervention will be delivered at ward level, and therefore, the ward will be considered the unit of analysis. Emergency, critical care, pediatric, maternity, peri-operative, operative rooms, and psychiatric areas will be excluded from the analysis, due to the fact that peripheral catheters are routinely maintained inserted for less than 24 h. Bias-compensating measures will be incorporated to homogenize nursing practice through face-to-face training in excluded wards.

### Sample/participants

All healthcare staff working on the study wards and delivering direct care to adult inpatients will be involved in the study. To ensure homogeneity between units, each ward enrolled in the study must have a stable permanent staff, reducing the possibility of contamination by personnel movement.

### Primary outcome measures: effect evaluation

The primary outcome will be the incidence of adverse events associated with the use of PVCs in adult inpatients. This incidence will be determined from evaluation of hospital records at 3, 6, 9, and 12 months.

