### Primary hypothesis

The implementation of a multimodal intervention will decrease the incidence of adverse events (CRBSI, extravasation, obstruction and phlebitis) associated with the use of PVCs in adult patients in hospital.

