### Secondary hypotheses

Nursing practice outcomes: An optimal fidelity of nurses to the recommendations within the CPG for insertion and management of peripheral venous catheter in hospital wards receiving the intervention will translate into reduced care variability, increased documentation about PVC use in nursing records and greater requests of catheter tip culture from PVCs removed from patients experiencing adverse events.Clinical outcomes: The fidelity of nurses to the recommendations within the CPG for insertion and management of peripheral venous catheter in hospital wards receiving the intervention will reduce unnecessary PVCs and decrease hospital length of stay (HLOS).Health economic outcomes: The implementation and development costs of the intervention will be offset by savings from decreased incidence of CRBSIs and HLOS.EBCP environment: The contextual and individual factors on the utilization of knowledge in clinical practice decisions and impact on hospital ward processes and practice measured by Nursing Work Index (NWI) [29] and Evidence-Based Practice Questionnaire (EBPQ) [30].

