### Secondary outcome measures: process evaluation

Nurses’ adherence to CPGs will be measured at 3, 6, 9, and 12 months with the following subcategories:1.1Multimodal intervention content will be delivered as planned (yes/no), and dosage will be delivered as often and long as planned (yes/no); face-to-face training session will be assessed by measuring the number of nurses who completed the Masterclass at the intervention phase. Feedback will be evaluated by checking the distribution of clinical audit results within intervention wards. Patient information will be assessed by monitoring the presence of informative leaflets on the ward (yes/no) and asking if the patient is aware of use of PVC and prevention recommendations for personal care. Facilitation will be measured by number of internal facilitators who completed the intervention.Clinical audits on use of PVC. Device utilization ratios will be measured by percentage of PVCs per hospital wards and number of PVC per patient. Documentation of PVC in nursing records will be assessed by percentage of fully completed records. PVC maintenance will be monitored by random, monthly clinical audits, which will document PVC size (16/18/20/22/24 gauge), site (dorsum of hand/forearm/antecubital region/upper arm), dressing integrity (clean/dry/intact), securement and time in situ (less 48 h/ between 48 and 96 h/more 96 h). Catheter tip will be measured by number of catheter tip extraction following removal of PVCs.Routine practice. Clinical effectiveness questionnaire for the prevention of PVC complications will be completed pre and post intervention. The questionnaire is made up of 35 questions in four sections, relating to general asepsis and skin antisepsis; PVC insertion, maintenance, and removal; PVC documentation; and patient and professional education.Clinical outcomes will be assessed using rates of unnecessary PVCs, rates of CRBSI, extravasation, obstruction and phlebitis, defined as per standard guidelines, and mean HLOS associated to PVC-BSIs at 3, 6, 9, and 12 months.The direct costs of implementing the multimodal intervention will be assessed using HLOS for patients and decrease rates of adverse events at 12 months (post intervention).EBCP environment:EBCP context: The contextual factors on the utilization of knowledge in clinical practice decisions and impact on hospital ward processes and practice will be assessed using the NWI tool pre-intervention. The variables are summarized into five main groups: nurses’ participation in hospital affairs; quality of nursing care; nurse management’s capacity, leadership, and support for nursing staff; size of the nursing workforce and adaptation of available human resources, and professional relation between doctors and nurses.EBCP individual: The opinions, attitudes, abilities and motivations of nurses and their links with the development of a culture of clinical practice based on the transfer of new knowledge to the healthcare given to patients will be assessed using EBPQ pre-intervention. The questionnaire is made up of 24 questions relating to professionals’ knowledge, use and attitudes towards EBCP.

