
### Sample size

Calculations are based on a previous observational pilot conducted in Manacor Hospital, which reported a global rate of 44.1% PVC-associated adverse events (16% phlebitis, 6.8% obstruction, 18.1% extravasation, and 3.2% CRBSIs rates of which 3.1% were CRBSIs type 1, 0.14% CRBSIs type 2, and none CRBSIs type 3). Similar studies have a potential for improvement between 7 and 19% in adverse event rates, such as phlebitis, infiltration, and obstruction, yet there is no statistical significance or potential for improvement in CRBSI rates [32, 33]. The initial assumption is for the intervention to decrease the rate of adverse events associated with PVC in the intervention group at 6 months post-intervention by 15%. For such target result, the sample size required would be 1920 nursing records, accepting an alpha risk of 0.05, a beta risk of 0.2 in a two-sided test, and 10% missing data. For the calculation of sample size, the smallest detectable difference with adequate power and statistical significance has been considered. The sample size has been corrected to account for within-intra cluster correlation coefficient of 0.01 to allow for a design effect of 1.99. The final sample size will therefore be of 3821 nursing records, assuming an average cluster size of 200 nursing records.

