### Data collection

To mitigate control bias, each nurse manager will be provided with information to standardize catheter removal, catheter tip culture, and hemoculture extraction. Tips from all PVC removed from patients experiencing adverse events will be cultured using a semiquantitative method. Clinical, microbiological, and ward information will be collected from each patient on PVC removal.

Project investigators will collect primary and secondary outcome data using a wide range of methods, including questionnaires NWI and EBPQ to nurses, clinical audits monthly, and clinical outcome by requesting statistics report the participating wards at each hospital with the variables. Where these data are not available, clinical outcome data will be adapted from our research to collect the primary and secondary outcome data. Tools will be used for communication between facilitators, auditors, and researchers to collect at the time of activity and throughout the duration of the intervention. The mean hospital length of stay for relevant wards will be collected as reported by the hospital electronic patient management systems. This data collection system was piloted in five of the above hospital units in December 2017. Adverse events will be defined as per international guidelines for the prevention of BSIs (Healthcare Infection Control Practices Advisory Committee, USA, UK, Spain) [46–48]. Three study phases will be planned for the PREBACP study: baseline (2 months), intervention and evaluation (12 months) (Fig. 2).

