### Definitions

CRSBI: The following case definitions will be used to determine a diagnosis of CRBSI (see Fig. 1):
▪CRBSI type 1: Local PVC-related infection (no positive blood culture): Positive quantitative culture (103 CFU/ml) or semi-quantitative culture with more than 15 CFU from the tip of PVC and local signs of infection at the insertion site or in catheter lumen.▪CRBSI type 2: General PVC-related infection (no positive blood culture positive): positive quantitative culture (103 CFU/ml) or semi-quantitative culture with more than 15 CFU from the tip of PVC and that clinical signs improve within 48 h of catheter removal.▪CRBSI type 3: PVC-BSI associated with microbiologically confirmed with blood culture occurring 48 h before or after catheter removal and positive quantitative culture (103 CFU/ml) or a semi-quantitative culture with more than 15 CFU from the tip of PVC for the same microorganism.
(b)Phlebitis: An inflammation of the wall of a vein. If a blood clot in the vein causes the inflammation, then the condition is termed thrombophlebitis. This problem is characterized by persistent pain referred to PVC (2 h since the last administration), erythema, swelling, and palpable thrombosis of the cannulated vein.(c)Extravasation: Inadvertent leakage of a vesicant solution into surrounding tissue.(d)Obstruction: Following occlusion of the PVC, which can be partial (i.e., blood cannot be aspirated, but PVC can be flushed) or complete, whereby neither aspiration nor infusion are possible.

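### Detection of the primary events may differ by arm, because they are taken from records that the intervention is itself expected to change

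*Protocol article*

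**What the plan says.** The primary hypothesis is that the intervention "will decrease the incidence of adverse events (CRBSI, extravasation, obstruction and phlebitis) associated with the use of PVCs" (Primary hypothesis). On the source of that incidence, the section on primary outcome measures says: "This incidence will be determined from evaluation of hospital records at 3, 6, 9, and 12 months". The sampling unit is the nursing record: "The final sample size will therefore be of 3821 nursing records" (Sample size).

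The Secondary hypotheses section says that intervention wards should show "increased documentation about PVC use in nursing records and greater requests of catheter tip culture from PVCs removed from patients experiencing adverse events". Both behaviours are then measured as adherence outcomes (Secondary outcome measures): "Documentation of PVC in nursing records will be assessed by percentage of fully completed records" and "Catheter tip will be measured by number of catheter tip extraction following removal of PVCs".

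Under Definitions, all three CRBSI types require a positive tip culture; type 1, for example, rests on a "semi-quantitative culture with more than 15 CFU from the tip of PVC and local signs of infection at the insertion site" or in the catheter lumen.

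The Data collection section contains partial safeguards. To limit bias, "each nurse manager will be provided with information to standardize catheter removal, catheter tip culture, and hemoculture extraction". It also says that tips are cultured for every catheter removed from a patient with an adverse event, and that clinical, microbiological and ward information is gathered for each patient when a catheter is removed.

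**The concern.** Two behaviours that the trial counts as process success can also affect whether a primary event is found. If nurses on intervention wards complete catheter records more fully, a larger share of true phlebitis, obstruction and extravasation may appear there. If they send more tips, more CRBSI may be confirmed. Using the same record system in both arms does not remove this, because what differs is how fully the system is used.

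The comparison would then mix a change in true incidence with a change in detection. A real reduction could be diluted or hidden, or a difference could appear where none exists. Blinding the analysts and research assistants does not help if the information first arises on wards that know they are receiving the intervention, and the Blinding section says that intervention wards are not blinded. An analysis plan cannot recover events that never reached the data, so this has to be settled where the outcome is defined.

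**Working it through.** **Inputs from the Sample size section.** Control incidence 44.1%, made up of phlebitis 16 + obstruction 6.8 + extravasation 18.1 + CRBSI 3.2. Fall of 15%. Two-sided alpha 0.05, power 80%, missing data 10%, design effect 1.99, 1920 records before and 3821 after the design effect. **Assumed, not in the protocol:** the ratio *r* of the share of true events recorded, intervention to control.

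**1. Reproduce the plan's figure.** A 15% relative fall gives 0.441 × 0.85 = 0.3749. The standard two-proportion formula (pooled variance under the null, no continuity correction) gives 866 per arm, 1732 in total. Dividing by 0.9 gives 1925, against 1920 stated. An absolute fall of 15 points gives only 358, so the relative reading is the one used. Then 1920 × 1.99 = 3821, as stated. Effective records per arm after missing data: 1920 × 0.9 / 2 = 864.

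**2. Effect of unequal recording.** With a fixed denominator, recorded RR = true RR × *r*. Hold recorded control incidence at 44.1% and set p₂ = 0.441 × 0.85 × *r*. With p̄ the mean of the two proportions,

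power = Φ{ [ |p₁ − p₂| √n − 1.96 √(2p̄(1 − p̄)) ] / √[p₁(1 − p₁) + p₂(1 − p₂)] }, n = 864.

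For *r* = 1.05: p₂ = 0.3936, and power = Φ{(0.0474 × 29.39 − 1.96 × 0.697) / 0.697} = Φ(0.04), about 52%.

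| *r* | recorded RR | power |
|---|---|---|
| 1.00 | 0.85 | 80% |
| 1.03 | 0.876 | 64% |
| 1.05 | 0.893 | 52% |
| 1.10 | 0.935 | 22% |
| 1.125 | 0.956 | 12% |
| 1.15 | 0.978 | 6% |
| 1/0.85 = 1.18 | 1.00 | effect cancelled |

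**3. Which route matters.** Phlebitis, obstruction and extravasation sum to 16 + 6.8 + 18.1 = 40.9 of 44.1 points. CRBSI is 3.2 / 44.1 = 7.3%. Suppose tips are sent in 70% of eligible removals in control wards and 90% in intervention wards (assumed), a ratio of 0.9 / 0.7 = 1.286, with everything else recorded equally. Intervention incidence is then 0.409 × 0.85 + 0.032 × 0.85 × 1.286 = 0.3826. The composite RR moves from 0.85 to 0.3826 / 0.441 = 0.87, and power falls to about 69%. Cancelling the effect through tips alone would need a ratio of (0.441 − 0.409 × 0.85) / (0.032 × 0.85) = 3.4.

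**4. Can the direction reverse?** Suppose poor recording also removes uneventful catheters from the denominator. Assume control wards record 90% of eventful and 80% of uneventful catheters, and intervention wards record 95% of both. Recorded control incidence is 0.441 × 0.90 / (0.441 × 0.90 + 0.559 × 0.80) = 0.470. Recorded intervention incidence stays at 0.375. Recorded RR = 0.375 / 0.470 = 0.80 for a true 0.85, so the effect is exaggerated.

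**5. Dependence on the design effect.** The stated ICC of 0.01 and cluster size of 200 give 1 + 199 × 0.01 = 2.99, not 1.99, which is a separate matter. With 2.99 there are 3821 × 0.9 / 2.99 / 2 = 575 effective records per arm, and power at *r* = 1 is already about 63%. The recorded RRs in the table do not change.

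**The case against.** A reader might infer more than the protocol supports, in three ways.

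*That recorded incidence must be biased against the intervention.* This does not follow. The hypothesis concerns documentation of catheter use, measured as completeness of records. More complete recording of events is a reasonable inference from that, not something the protocol states, and step 4 shows that the sign can turn.

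*That an event exists only if a ward nurse wrote it down.* The protocol refers to hospital records, and Data collection describes several methods, including monthly audits and information gathered at removal. What stands is that the outcome definition is not tied to the removal data, and that the sample is counted in nursing records.

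*That tip culture could by itself overturn the primary result.* With 70% against 90% of tips sent, a true CRBSI ratio of 0.85 would appear as 0.85 × 1.286 = 1.09, but that is one component; the composite moves only to 0.87. The route is also partly addressed, since nurse managers receive standardising information with no stated restriction by arm and all tips from patients with adverse events are to be cultured. The four component rates sum exactly to 44.1%, so a positive tip may only reclassify an event already counted; the protocol does not settle this. Still, if every such tip were cultured in both arms, the hypothesised rise in requests on intervention wards could not occur. The two sections need reconciling.

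Also fair: every recording ratio used here is assumed, and sensitivity analyses are commonly left to an analysis plan. The source and definition of the primary event, however, are fixed in this document. Its safeguards cover removal and cultures; none equalises the recording of phlebitis, extravasation or obstruction.

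**Conclusion.** The point holds as one of possible differential ascertainment: the protocol takes its primary outcome from records while expecting catheter documentation and tip requests to rise in one arm only. The likely direction is against the intervention, but it is not certain. Recording of the three non-CRBSI events is the main route; tip culture is minor for the composite and partly mitigated. The comparison is sensitive to small differences: a relative recording gain of 5% costs about 28 points of power (80% to 52%), and a gain of about 18% cancels the planned effect. These figures assume a fixed denominator, 44.1% recorded in controls, a true relative fall of 15% and the stated design effect of 1.99. The true recording ratio cannot be learned from the document. The change should be made, because it is cheap and concerns the validity of the primary outcome.

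**What to change.** 1. In the section on primary outcome measures, define the primary event from the information already planned at each catheter removal, with an obligatory yes/no for CRBSI, phlebitis, extravasation and obstruction. Use the identical form in both arms and start it in the 2-month baseline, so that recording can settle before the comparison begins.
2. Use all removed catheters as the denominator. Treat a blank as missing, not as event-free.
3. Report record completeness (already a secondary measure) and the share of eligible tips cultured, by arm.
4. Pre-specify a tipping analysis over recording ratios on both sides of 1, for example 0.9 to 1.2. An obligatory field ensures an entry but not equal recognition of signs, so this is still needed.
5. Reconcile the hypothesis of more tip requests on intervention wards with the statement that all tips from patients with adverse events are cultured.

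Do not restrict the primary comparison to fully completed records: completeness is something the intervention is meant to change, so the restriction would bring in a new bias. For the same reason, give CRBSI per cultured tip as a description only.

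Cost: protocol wording, one obligatory field set on data collection already planned, and one sensitivity analysis. Some records will move from no event to missing.

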### Secondary outcome measures: process evaluation

Nurses’ adherence to CPGs will be measured at 3, 6, 9, and 12 months with the following subcategories:1.1Multimodal intervention content will be delivered as planned (yes/no), and dosage will be delivered as often and long as planned (yes/no); face-to-face training session will be assessed by measuring the number of nurses who completed the Masterclass at the intervention phase. Feedback will be evaluated by checking the distribution of clinical audit results within intervention wards. Patient information will be assessed by monitoring the presence of informative leaflets on the ward (yes/no) and asking if the patient is aware of use of PVC and prevention recommendations for personal care. Facilitation will be measured by number of internal facilitators who completed the intervention.Clinical audits on use of PVC. Device utilization ratios will be measured by percentage of PVCs per hospital wards and number of PVC per patient. Documentation of PVC in nursing records will be assessed by percentage of fully completed records. PVC maintenance will be monitored by random, monthly clinical audits, which will document PVC size (16/18/20/22/24 gauge), site (dorsum of hand/forearm/antecubital region/upper arm), dressing integrity (clean/dry/intact), securement and time in situ (less 48 h/ between 48 and 96 h/more 96 h). Catheter tip will be measured by number of catheter tip extraction following removal of PVCs.Routine practice. Clinical effectiveness questionnaire for the prevention of PVC complications will be completed pre and post intervention. The questionnaire is made up of 35 questions in four sections, relating to general asepsis and skin antisepsis; PVC insertion, maintenance, and removal; PVC documentation; and patient and professional education.Clinical outcomes will be assessed using rates of unnecessary PVCs, rates of CRBSI, extravasation, obstruction and phlebitis, defined as per standard guidelines, and mean HLOS associated to PVC-BSIs at 3, 6, 9, and 12 months.The direct costs of implementing the multimodal intervention will be assessed using HLOS for patients and decrease rates of adverse events at 12 months (post intervention).EBCP environment:EBCP context: The contextual factors on the utilization of knowledge in clinical practice decisions and impact on hospital ward processes and practice will be assessed using the NWI tool pre-intervention. The variables are summarized into five main groups: nurses’ participation in hospital affairs; quality of nursing care; nurse management’s capacity, leadership, and support for nursing staff; size of the nursing workforce and adaptation of available human resources, and professional relation between doctors and nurses.EBCP individual: The opinions, attitudes, abilities and motivations of nurses and their links with the development of a culture of clinical practice based on the transfer of new knowledge to the healthcare given to patients will be assessed using EBPQ pre-intervention. The questionnaire is made up of 24 questions relating to professionals’ knowledge, use and attitudes towards EBCP.

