### Control group

The control ward will not receive the multimodal intervention and will continue with routine practice.

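### The tip-culture measure is a count with no denominator, so the fall in adverse events that the trial hopes for biases it against its own hypothesis

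*Protocol article*

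**What the plan says.** Four parts of the protocol article bear on this point.

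- **Secondary hypotheses** (nursing practice outcomes) predicts, for intervention wards, "greater requests of catheter tip culture from PVCs removed from patients experiencing adverse events". This is a statement about catheters that had an event.
- **Secondary outcome measures: process evaluation** fixes the measure: "Catheter tip will be measured by number of catheter tip extraction following removal of PVCs". No denominator is named, and the count is not limited to catheters with an event. A neighbouring item in the same list does have one: "Documentation of PVC in nursing records will be assessed by percentage of fully completed records".
- **Data collection** says that "each nurse manager will be provided with information to standardize catheter removal, catheter tip culture, and hemoculture extraction", and then: "Tips from all PVC removed from patients experiencing adverse events will be cultured using a semiquantitative method". Neither sentence is limited to one arm.
- **Primary hypothesis** states: "The implementation of a multimodal intervention will decrease the incidence of adverse events".

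For comparison, **Control group** says: "The control ward will not receive the multimodal intervention and will continue with routine practice".

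**The concern.** The hypothesis concerns how often nurses request a culture when a catheter is removed from a patient with an adverse event. The measure records how many tips are taken. The two agree only if both arms have the same number of event catheters, and the trial is designed to make those numbers differ. Better requesting pushes the intervention count up, while fewer events push it down. The same section of secondary hypotheses also expects fewer unnecessary catheters, which would further lower the number of removals from which tips can be taken.

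The common instruction in Data collection adds a second difficulty. The closer all wards come to culturing every event tip, the smaller the difference in requesting that is left to find, and the more the count simply follows the event rate.

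At stake is the reading of a process measure. A ward group that improved its requesting and prevented events could show the lower count. There is also a link to the primary outcome: under Definitions, all three CRBSI types require a positive tip culture. Whether tips are cultured equally often in both arms therefore matters for comparing CRBSI, and a raw count does not show it.

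**Working it through.** **Step 1. Which effect size the plan uses.** Inputs from Sample size: a "global rate of 44.1% PVC-associated adverse events", a 15% decrease, two-sided alpha 0.05, beta 0.2 and 10% missing data. The usual two-proportion formula is

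n per arm = [1.96 × √(2p̄(1−p̄)) + 0.8416 × √(p₁(1−p₁) + p₂(1−p₂))]² / (p₁−p₂)²

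- Relative reading: p₂ = 0.441 × 0.85 = 0.375. This gives n = 866 per arm, 1732 in total, and 1732/0.9 = 1925 with missing data. The plan states 1920, so it reproduces.
- Absolute reading: p₂ = 0.441 − 0.15 = 0.291. This gives 161 per arm, 322 in total, and 358 with missing data. It does not reproduce.

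The relative reading is used below. The plan's 1920 × 1.99 = 3820.8 gives its final 3821 records.

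**Step 2. Expected tip counts.** The plan gives no figure for this measure. Allocation is 1:1, so there are about 3821/2 ≈ 1910 records per arm. Assume one catheter outcome per record and no overlap between event types. Let c be the share of event tips that is cultured.

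Expected tips = 1910 × event rate × c

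With every event tip cultured (c = 1 in both arms):

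- Control: 1910 × 0.441 = 842
- Intervention: 1910 × 0.37485 = 716

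The ratio is 716/842 = 0.85. The count is 15% lower although requesting is identical and complete.

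**Step 3. What is needed to tie or to exceed.** The count ratio is 0.85 × (c intervention / c control).

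- Tie: c intervention / c control = 1/0.85 = 1.18.
- Since c intervention cannot exceed 1, the intervention count cannot exceed control once c control is above 0.85.

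**Step 4. Range over assumed culture shares.** The documents give no shares, so these are illustrations.

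| Control cultured | Intervention cultured | Control tips | Intervention tips | Direction of count |
|---|---|---|---|---|
| 100% | 100% | 842 | 716 | lower, with equal practice |
| 90% | 100% | 758 | 716 | lower, with better practice |
| 70% | 80% | 590 | 573 | lower, with better practice |
| 60% | 80% | 505 | 573 | higher, as hypothesised |
| 50% | 80% | 421 | 573 | higher, as hypothesised |

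A modest improvement in requesting is reversed. A large one survives, but is understated: 80% against 60% is a ratio of 1.33 in requesting and only 573/505 = 1.13 in the count.

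**Step 5. The proportion instead.** Dividing by event catheters returns the culture share itself in every row (for example 100% v 100%, or 80% v 70%), whatever the event rate.

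**The case against.** A reader might infer that the hypothesis cannot be tested at all, because all event tips are to be cultured in both arms. The documents do not support that. Nurse managers are given information; nothing says that every ward nurse complies, and control wards otherwise keep their routine practice. With incomplete compliance on control wards, a large difference in requesting still shows in the count, as the last two rows of the table demonstrate. That control wards are covered is itself an inference. It is a strong one, since the instruction goes to each manager with the declared aim of mitigating control bias, but it is not written out.

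A reader might also take the 15% as percentage points and find a larger distortion. That reading gives about 358 records against the stated 1920, so it should not be used.

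Other objections partly stand.

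- The 44.1% is the sum of the component rates (16 + 6.8 + 18.1 + 3.2). A catheter with two events may be counted twice, and a record may cover more than one catheter. The absolute counts are therefore approximate. The 0.85 ratio holds if overlap and catheters per record are similar in the two arms.
- The measure refers to catheter removals in general. If tips from catheters without an event are also taken, the count does not track the event rate exactly. It is then still further from the hypothesis, which concerns event catheters only.
- Event rates are reported at the same time points and clinical and microbiological data are gathered at removal, so a careful analyst could form the proportion. That makes the problem easy to correct, but the stated measure remains a count.
- An article may leave a denominator to a fuller document. Here, however, the article itself specifies a number, and gives a percentage for the neighbouring documentation item.

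**Conclusion.** The point holds as a mismatch between hypothesis and measure. The count is biased against the tip-culture hypothesis whenever the primary hypothesis is true. At the plan's own effect size the bias is a factor of 0.85: about 842 against 716 tips at equal, complete culturing, a required 1.18-fold higher culture share to tie, and no possibility of a higher intervention count once control cultures more than about 85%. The counts rest on one catheter outcome per record, non-overlapping events, 1:1 allocation of 3821 records, and tips being taken from event catheters. The ratio does not depend on the number of records.

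The hypothesis is distorted, not untestable. The common culture instruction shrinks the contrast it expects, to an extent that depends on compliance, which the documents do not give. Severity is minor: this is a secondary process measure with no sample size attached. The link to CRBSI ascertainment is real but limited for the composite, as CRBSI contributes 3.2 of the 44.1 points (3.2/44.1 = 7%). It matters more for CRBSI reported separately.

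**What to change.** - In Secondary outcome measures, replace the number of tips with a proportion. The numerator is catheters removed with an adverse event whose tip was sent for culture. The denominator is all catheters removed with an adverse event. Report it by arm at 3, 6, 9 and 12 months. A binary measure of this kind also fits the generalized estimating equation models already planned for rate outcomes.
- Report the same proportion as a check that CRBSI was ascertained equally in the two arms.
- Reconcile Secondary hypotheses with Data collection. State whether the common instruction covers control wards and, if it does, what between-arm difference in requesting is still expected. Keeping the hypothesis is defensible if compliance is expected to be incomplete; dropping it is a choice for the investigators.

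The cost is a few sentences. Adverse events are already recorded for the primary outcome and tips are already counted. The one practical requirement is that tip culture and event status can be linked for each catheter, and the planned collection of clinical and microbiological data at removal should allow this.
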